### Sample size

A power analysis (G*Power; version 3.9.1.4) revealed that a sample size of 22 participants in each group (IG 1; IG 2; WG), with at least two repeated measurements would enable detection of a medium effect size (*d* = 0.50) [78], with power of 0.95 and alpha of 0.05. A total sample size of 66 participants is therefore required.

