**Methods:**

The proposed study comprises a cluster randomised controlled trial that will be conducted in at least three secondary vocational schools, to which teachers will be recruited from three types of courses: Care, Technology, and Economy. The allocation of the intervention programme to the participating schools will be randomised. The teachers from each school will be assigned to intervention group 1 (IG 1), intervention group 2 (IG 2), or the waiting list group (WG). IG 1 will receive MBSR training and IG 2 will receive MBSR training combined with an additional organisational health intervention. WG, that is the control group, will receive MBSR training one year later. The primary outcome variable of the proposed study is mindfulness, which will be measured using the Dutch version of the Five Facet Mindfulness Questionnaire (FFMQ-NL). In the conceptual model, the effects of teachers’ mindfulness resulting from the intervention programmes (MBSR training and MBSR training combined with an additional organisational health intervention) will be related to salient (secondary outcome) variables: mental health outcomes (e.g., burnout, work engagement), work performance, work-related perceptions (job demands and job resources), and personal competencies (e.g., occupational self-efficacy). Data will be collected before (T_0_) and immediately after the MBSR training (T_1_), and 3 (T_2_) and 9 months (T_3_) after the training. The power analysis revealed a required sample size of 66 teachers (22 in each group).

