## Discussion

The proposed study will evaluate the short-term (T_1_) and long-term effects (T_2_ and T_3_) of mindfulness-based stress reduction (MBSR), a person-focused intervention aimed at strengthening the individual capacity of teachers in secondary vocational schools to cope with stress and enhance their mental health. In addition, the possible enhancing effects of an additional organisational health intervention, a participatory action approach, will be investigated as well. The teachers’ experiences with the interventions (the working mechanisms of MBSR and the organisational health intervention) will also be examined. This study is a cluster randomised controlled trial, in which intervention group 1 (IG 1; receiving MBSR) and intervention group 2 (IG 2; receiving MBSR and an additional organisational health intervention) will be compared with the waiting list group (WG; the control group).

Many previous studies on the effects of MBSR on employees have primarily assessed negative outcomes, focusing predominantly on mental health (e.g., burnout, stress level, psychological distress). Process measures, which are suitable for investigating how mindfulness can contribute to well-being, have rarely been assessed [19]. The strength of this study lies in the fact that we will assess both negative and positive outcomes. More specifically, it considers not only mental health (e.g., positive emotions at work, work engagement, organisational commitment), but also work performance and work-related perceptions (e.g., job demands and job resources). Process measures (e.g., occupational self-efficacy, taking distance) will also be examined. Hence a wide range of outcomes will be measured [19].

In their systematic review on MBSR and employees’ mental health, Janssen et al. [19] reported that 14 of the 23 studies included in the review only incorporated short-term effects, measured immediately after the intervention. However, in terms of the cost-benefit ratio, MBSR and the organisational health intervention should lead to sustainable long-term effects. Therefore, another strength of this study is that it will gather longitudinal data by measuring both short-term and long-term effects (until 9 months after the intervention).

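### The stated 0.95 power for d = 0.50 with 22 teachers per group does not reproduce under standard settings; the total of 66 fits a between-arm difference of about 1.06 to 1.22 SD

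*Protocol article*

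**What the plan says.** The Sample size section reports a calculation in G*Power ("A power analysis (G*Power; version 3.9.1.4"). Its basis is "a sample size of 22 participants in each group (IG 1; IG 2; WG), with at least two repeated measurements". The claim made for that number is that it "would enable detection of a medium effect size", which the section gives as d = 0.50. The error rates attached to the claim are stated as "with power of 0.95 and alpha of 0.05". The section then concludes: "A total sample size of 66 participants is therefore required". The abstract repeats the number without an effect size or power: "The power analysis revealed a required sample size of 66 teachers (22 in each group").

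The section does not name the test, say whether it is one- or two-sided, or give the correlation between measurements. The Statistical analyses section plans longitudinal regression or a repeated-measures model, with the T0 value as an independent variable and T1 to T3 as dependent variables. The Discussion gives the contrast of interest: IG 1 and IG 2 "will be compared with the waiting list group (WG; the control group").

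**The concern.** In a comparison of arms, d = 0.50 normally means a difference of half a standard deviation. Detecting that with 0.95 power usually takes about 100 participants per arm, so 22 is far too few unless repeated measurement removes most of the variance. The section mentions repeated measurement but gives no correlation that would do so.

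This is the article's only power statement. If a comparison with the waiting list on the mindfulness score is not significant, a reader would take it that a medium effect had been excluded with high probability. If the calculation was really made for an effect about twice that size, the inference would be unsound.

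**Working it through.** **Inputs from the article.** 3 groups, 22 per group, N = 66, at least 2 measurements, d = 0.50, power 0.95, alpha 0.05. **Assumed, because not stated:** two-sided tests, correlation r between measurements, common SD, no clustering and no drop-out.

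**1. Reproducing 66.** For a repeated-measures within-between interaction with k = 3 groups and m = 2 measurements:

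lambda = f² × N × m / (1 − r), with df = (k − 1)(m − 1) and (N − k)(m − 1).

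With f = 0.25 and r = 0.5, lambda = 0.0625 × 66 × 2 / 0.5 = 16.5 on 2 and 63 df.

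- N = 66: power 0.953
- N = 63 (next smaller balanced total): power 0.944

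So 66 is the smallest balanced total that reaches 0.95 under these entries. A one-way ANOVA with f = 0.50 has the same noncentrality (0.25 × 66 = 16.5) and df, and so also gives 66.

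**2. What f = 0.25 means in that test.** With two measurements, f is half the SD of the three groups' mean changes, in units of the outcome SD. So f = 0.25 means that the mean changes have an SD of 0.50.

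- Pattern 0, D, D (both active arms equally effective): SD = D × √(2/9) = 0.4714 D, so D = 0.50 / 0.4714 = 1.06.
- Pattern 0, D/2, D (evenly spaced): SD = 0.4082 D, so D = 0.50 / 0.4082 = 1.22.

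This conversion does not involve r. The one-way ANOVA route, with f = 0.50 as the SD of the group means, implies the same two values.

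**3. Power for a true d = 0.50 with 22 per group.**

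| Reading | Power |
|---|---|
| Two arms, unadjusted, one time point | 0.37 (0.95 needs 105 per group) |
| Pre-post within one group, paired, standardised change 0.50 | 0.61 (0.95 needs 54) |
| Two arms, one follow-up adjusted for baseline, r = 0.5 | 0.46 |
| Same, r = 0.7 | 0.62 |
| Same, r = 0.8 | 0.77 |
| Two arms, mean of three follow-ups adjusted for baseline; follow-up correlation 0.7, baseline correlation 0.5 | 0.59 |
| Same, baseline correlation 0.7 | 0.83 |
| Three-group, two-measurement interaction, r = 0.5, pattern 0, 0.5, 0.5 (f = 0.118) | 0.37 |
| Same, pattern 0, 0.25, 0.5 (f = 0.102) | 0.29 |

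For the adjusted rows the effect is 0.50 divided by the residual SD. The residual variance is 1 − r² for one follow-up. For the mean of three it is (1 + 2 × 0.7)/3 − r² = 0.80 − r², which is 0.55 at r = 0.5 and 0.31 at r = 0.7.

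**4. Correlations at which d = 0.50 does reach 0.95.**

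- Two-measurement interaction: r of about 0.889 (pattern 0, 0.5, 0.5) or 0.917 (pattern 0, 0.25, 0.5).
- One follow-up: at r = 0.90, power is 0.95 on change scores and 0.96 adjusted for baseline.
- Mean of three follow-ups, adjusted for baseline, all correlations equal: r of about 0.83 (power 0.954).

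For scale, the Primary outcome section quotes an internal consistency of 0.85 for the total mindfulness score in non-meditators. That is a rough ceiling for a between-visit correlation, not a strict bound. At r = 0.85 a single follow-up gives 0.84 (change score) to 0.87 (baseline-adjusted).

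**The case against.** The strongest reply is that the article leaves the correlation open and speaks of at least two measurements, while the design has a baseline and three follow-ups. With strong correlations the claim can be met: about 0.83 throughout if the follow-ups are averaged with baseline adjustment, or about 0.9 with two measurements. This stands, and it rules out saying that no reading of d = 0.50 gives 0.95. It does not rescue the sentence as written, which rests on two measurements and states no such correlation.

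A reader might also infer three stronger things that the article does not support.

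- **That f = 0.25 was certainly entered in place of d = 0.50.** The match is exact and both values carry the label medium, but the inputs are not stated and one-way ANOVA with f = 0.50 gives the same total.
- **That 0.37 is the power of the planned analysis.** The three-group, two-measurement interaction is a reconstruction. The article plans a longitudinal analysis with T0 as an independent variable, for which the baseline-adjusted figures are closer.
- **That the trial would miss a medium effect more often than not.** That holds for the unadjusted comparison and for one follow-up at r = 0.5. It fails at r = 0.7 (0.62) and for averaged follow-ups (0.59 to 0.83).

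Finally, an article may leave calculation details to a fuller document. The point here is the stated result, not the missing detail.

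**Conclusion.** The claim of 0.95 power for d = 0.50 is wrong as written: the design does not deliver it under ordinary assumptions. With moderate correlations (0.5 to 0.7), power for a between-arm d = 0.50 runs from about 0.37 to about 0.83, depending on baseline adjustment and on how many follow-ups are combined. The effect size that fits 66 at 0.95 is a between-arm difference of about 1.06 to 1.22 SD, roughly twice the one named.

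The power figures rest on assumed correlations, two-sided tests and equal variances, and they ignore clustering and drop-out, both of which would lower power. The attribution to f = 0.25 with correlation 0.5 is an inference from the exact match. The conversion from f = 0.25 to 1.06 or 1.22 SD does not depend on the correlation.

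**What to change.** In the Sample size section, remove the statement that 22 per group gives 0.95 power for d = 0.50, and state the G*Power test, the effect metric and the correlation actually entered.

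If the entries were f = 0.25 and correlation 0.5 in the three-group, two-measurement interaction, say the following:

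- A total of 66 gives 0.95 power for a difference in change from the waiting list of about 1.06 SD if both active arms work equally, or a range of about 1.22 SD if the arms are evenly spaced.
- Before clustering and drop-out, power for a between-arm d = 0.50 is about 0.37 unadjusted, 0.46 to 0.62 at one baseline-adjusted follow-up (r = 0.5 to 0.7), and about 0.59 to 0.83 for three averaged follow-ups (follow-up correlation 0.7, baseline correlation 0.5 to 0.7).

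If other entries were used, give them and the between-arm difference they imply. In either case, commit to interpreting non-significant comparisons from confidence intervals and not from the planned power.

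The cost is wording and a less favourable stated figure. The enrolment figure of 66, including in the abstract, can stay.

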### Cluster randomisation

A CRCT is a randomised controlled trial in which groups of subjects (i.e., schools) are randomised rather than individual subjects (i.e., teachers) [48]. Cluster randomisation will be performed at the school level. This will provide the researchers with the opportunity to study the effects of an additional organisational health intervention that cannot be directed towards selected individuals (i.e., teachers) and to control for “contamination” across individuals (i.e., the effects on one teacher may influence the effects on another teacher in the same course) [49]. In the first secondary vocational school (known as an MBO in Dutch), participating teachers from one course (Care, Technology, or Economy) will be assigned to intervention group 1 (IG 1: MBSR), teachers from another course will be assigned to intervention group 2 (IG 2: MBSR and an additional organisational health intervention), and teachers from the third course will be assigned to the waiting list group (WG). The allocation will be different at each school (see Table 3). A researcher who is not involved in assigning courses/participants to the groups will prepare concealed, consecutively numbered, sealed opaque envelopes. Every envelope will contain a paper indicating the treatment assignment at school level (type 1, 2 or 3). The MBO schools will receive their envelopes from a researcher who is unaware of the randomisation sequence. The MBO schools can open the envelope in the presence of the researcher and the researcher will be informed about the treatment assignment.

**Table 3 Tab3:** Cluster randomisation

	Care	Technology	Economy
**MBO school, type 1**	IG 1^a^	IG 2^b^	WG^c^
**MBO school, type 2**	WG	IG 1	IG 2
**MBO school, type 3**	IG 2	WG	IG 1

^a^ IG 1: intervention group 1 (MBSR)

^b^ IG 2: intervention group 2 (MBSR and an additional organisational health intervention)

^c^ WG: waiting list group (control group that will receive MBSR one year later)

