Data from questionnaires using self-reports may be biased [85]. The primatologist and psychologist De Waal [86] posited that human beings are insufficiently aware of their inner state and may therefore mislead themselves and others. The study of the human psyche needs behavioural reports, based on observation by others [86]. The proposed study will address this concern partly by using both validated questionnaires and data triangulation (both quantitative and qualitative data).

Another potential source of bias is associated with the effect of attention received by teachers in IG 1 and IG 2, also known as the Hawthorne effect [35]. Participating in group sessions in IG 1 and IG 2 may lead to an overestimation of the effect of MBSR and the organisational health intervention. Participants cannot be blinded to the allocated intervention, so the Hawthorne effect cannot be excluded.

The proposed CRCT has some disadvantages compared to an RCT [87]. A CRCT has greater complexity in design and analysis and requires more participants/teachers, to achieve adequate statistical power.

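### The 66 teachers for 0.95 power is a figure for independent teachers: it has no allowance for clustering, although whole courses within schools are allocated and the Discussion says a cluster trial needs more participants

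*Protocol article*

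**What the plan says.** All references are to the protocol article.

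- **Sample size.** One G*Power analysis is reported. Twenty-two teachers in each of three groups, "with at least two repeated measurements", "would enable detection of a medium effect size" (d = 0.50), "with power of 0.95 and alpha of 0.05". It concludes: "A total sample size of 66 participants is therefore required". The Abstract repeats 66 (22 per group) as the required number, without the power. The section gives no ICC, design effect, number of clusters or cluster size.
- **Cluster randomisation.** "Cluster randomisation will be performed at the school level". Each school draws one of three fixed patterns (Table 3). Within a school, "participating teachers from one course (Care, Technology, or Economy) will be assigned to intervention group 1", a second course goes to the other intervention group and the third to the waiting list. The section also recognises that teachers in the same course may affect one another.
- **Participants and recruitment.** At least three schools, with three courses in each.
- **Statistical analyses.** GEE, mixed models or a repeated-measures general linear model. No denominator degrees of freedom are given.
- **Discussion.** Compared with an individually randomised trial, a cluster trial "requires more participants/teachers, to achieve adequate statistical power".

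**The concern.** The article treats teachers within a course as dependent when it justifies the design, and says in the Discussion that this dependence raises the number needed. The Sample size section nevertheless presents an unadjusted number as the requirement. The two statements do not fit together.

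The unit that receives an arm is a course within a school. Teachers in such a cell share a department and, in the group with the organisational intervention, an intervention aimed at the course as a whole. Some positive correlation in their change in mindfulness is therefore plausible. If it exists, 66 teachers carry less information than the calculation credits. A reader who relies on the stated 0.95 would then take a null result as stronger evidence against a medium effect than it is.

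**Working it through.** **Inputs from the article:** 3 groups, N = 66, two measurements (the stated minimum), alpha 0.05, power 0.95, d = 0.50, at least 3 schools with 3 courses each.

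**Inputs assumed:** f = 0.25, from f = d/2; correlation between repeated measurements ρ = 0.5 (the G*Power default); every ICC value below.

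**Step 1. Reproduce the 66.** For the group-by-time interaction in a repeated-measures ANOVA with k groups and m measurements:

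- λ = f² × N × m / (1 − ρ)
- df1 = (k − 1)(m − 1), df2 = (N − k)(m − 1)

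At N = 66: λ = 0.0625 × 66 × 2 / 0.5 = 16.5, df1 = 2, df2 = 63, power 0.9535. At N = 63 power is 0.9436. So 66 is the smallest balanced total that reaches 0.95. With the same f, two measurements and ρ, the between-groups test needs 189 and the within-subjects test 57, so neither gives 66. The error df of 63 count every teacher as independent, and there is no spare margin that could be a cluster allowance.

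**Step 2. Clusters at the stated minimum.** 3 schools × 3 courses = 9 cells, 3 per arm, mean size 66/9 = 7.33.

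**Step 3. Apply the design effect.** DE = 1 + (7.33 − 1) × ICC, and λ becomes 16.5/DE. Power is shown first on the calculation's own 63 df. It is then shown on 9 − 3 = 6 df, as a conservative bound from a cell-level test that the plan does not specify.

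| ICC (assumed) | DE | λ | Power, 63 df | Power, 6 df |
|---|---|---|---|---|
| 0.01 | 1.06 | 15.5 | 0.94 | 0.77 |
| 0.02 | 1.13 | 14.6 | 0.93 | 0.75 |
| 0.05 | 1.32 | 12.5 | 0.88 | 0.68 |
| 0.10 | 1.63 | 10.1 | 0.80 | 0.58 |

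**Step 4. More schools, same 66 teachers.** With six schools there are 18 cells of 3.67 teachers, and cell-level df are 18 − 3 = 15.

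| ICC (assumed) | DE | Power, 63 df | Power, 15 df |
|---|---|---|---|
| 0.02 | 1.05 | 0.94 | 0.90 |
| 0.05 | 1.13 | 0.93 | 0.88 |
| 0.10 | 1.27 | 0.89 | 0.84 |

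**Step 5. Sensitivity to the assumed correlation.** With 9 cells, ICC 0.05 and 63 df, power is 0.81, 0.88, 0.94 and 0.985 at ρ = 0.4, 0.5, 0.6 and 0.7. Only ρ = 0.5 among the nearby values returns 66 as the required total: ρ = 0.4 would require 78, and ρ = 0.6 would require 54.

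**The case against.** The strongest reply is that the size of the loss is not fixed by anything in the article.

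- **No ICC or correlation is stated.** At ICC 0.01 the design effect costs about one point of power, and a correlation above 0.5 would offset part of the loss. This stands: the figures are a range under assumptions. It does not touch the finding that 66 contains no allowance.
- **Four measurements are planned, two are the floor.** The same formula with four occasions gives 0.99, 0.98 and 0.93 at ICC 0.02, 0.05 and 0.10 on individual-level df. But holding f fixed over four occasions is a different alternative hypothesis, so this does not support the stated 0.95 at 66.
- **Nine cells is a minimum, and every school contains all three arms.** Both points stand. More schools shrink the loss (Step 4), and additive school effects largely cancel. What remains is correlation among teachers of one course within a school.
- **GEE or mixed models can handle clustering.** They can correct the standard errors, but they do not restore the power.

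Some stronger readings are tempting but not supported:

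- A reader might infer that the trial's power is that of a test on 6 df, or on only 2 df once school and course are also fitted. The Statistical analyses section specifies neither test and says only that confounders will be corrected for. The 6-df column is a bound. Part of its drop comes from the choice of test, since it gives 0.80 even at ICC 0.
- A reader might infer that teachers in every cell share an MBSR group and trainer. Waiting-list cells receive MBSR only after one year, and the article does not say that training groups are formed by course.
- A reader might add the question of what d = 0.50 means for a comparison of two arms. That is a separate issue and is not needed here.

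**Conclusion.** The point holds. The arithmetic behind 66 is not wrong, but it answers the question for independent teachers. On its own inputs, it does not deliver 0.95 under the allocation described once teachers in a cell are positively correlated, and it conflicts with the Discussion's statement that a cluster trial needs more participants.

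On the design effect alone, with nine cells, power goes from 0.95 to between 0.94 and 0.80 for ICC 0.01 to 0.10. With 18 cells it is 0.94 to 0.89 for ICC 0.02 to 0.10. A conservative cell-level test would give 0.77 to 0.58 with nine cells, and 0.90 to 0.84 with 18 cells over ICC 0.02 to 0.10. All of this rests on f = 0.25, two measurements, an assumed correlation of 0.5 and assumed ICCs. That 66 is the individual-level figure is a strong inference from exact reproduction; the article does not say so. A reader might conclude that the trial is known to be badly underpowered. The article does not support that, because it gives neither the ICC nor the final number of cells.

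**What to change.** Change the wording in the Sample size section:

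- state that 66 and 0.95 assume independent teachers;
- name the course-by-school cell as the cluster;
- restate the power using the actual number of cells, an ICC range with its justification, the repeated-measures correlation used and the degrees of freedom of the planned model.

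Qualify the word "required" for 66 both there and in the Abstract. The Abstract does not give 0.95, so only the number needs qualifying there. The powers worked out above rest on assumed inputs and should not be copied into the protocol as results.

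The cost is a short recalculation and a less favourable stated power. No added recruitment is asked for: the Trial status section puts the first randomisation in September 2016 and the last assessments in June 2020.

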### Blinding

Participants, trainers, facilitator, and researchers cannot be blinded to their assigned intervention after cluster randomisation. All participants have to fill in the online questionnaire at home or at work, excluding the influence of the researcher. The developer of the online questionnaire will collect the data and provide the anonymous data to the researcher. The researcher will analyse the data blinded to the assigned intervention.

